## Abstract

**Background:**

Periodontitis is a common, chronic inflammatory disease caused by gram-negative bacteria leading to destruction of tissues supporting the teeth. Epidemiological studies have consistently shown increased frequency, extent and severity of periodontitis among diabetic adults. More recently, some controlled clinical trials have also suggested that periodontal treatment could improve glycaemic control in diabetic patients. However current evidence does not provide sufficient information on which to confidently base any clinical recommendations. The main objective of this clinical trial is to assess whether periodontal treatment could lead to a decrease in glycated haemoglobin levels in metabolically unbalanced diabetic patients suffering from chronic periodontitis.

**Methods:**

The DIAPERIO trial is an open-label, 13-week follow-up, randomized, controlled trial. The total target sample size is planned at 150 participants, with a balanced (1:1) treatment allocation (immediate treatment vs delayed treatment). Periodontal treatment will include full mouth non-surgical scaling and root planing, systemic antibiotherapy, local antiseptics (chlorhexidine 0.12%) and oral health instructions. The primary outcome will be the difference in change of HbA1c between the two groups after the 13-weeks' follow-up. Secondary outcomes will be the difference in change of fructosamine levels and quality of life between the two groups.

**Discussion:**

The DIAPERIO trial will provide insight into the question of whether periodontal treatment could lead to an improvement in glycaemic control in metabolically unbalanced diabetic patients suffering from periodontitis. The results of this trial will help to provide evidence-based recommendations for clinicians and a draft framework for designing national health policies.

**Trial registration:**

Current Controlled Trials ISRCTN15334496

## Background

Periodontitis is a common, chronic inflammatory disease caused by gram-negative infection leading to the destruction of tissues supporting the teeth. Approximately 50% of adults in the United States have chronic periodontitis [1] and similar rates have been reported in France [2].

Diabetes is a metabolic disorder characterized by high blood glucose levels. It is a significant cause of morbidity and mortality in both developed and developing countries. Its prevalence for all age-groups worldwide has been estimated at 2.8% in 2000 and 4.4% in 2030 [3].

The relationship between these two affections has been largely described in the literature over the past 50 years. Epidemiological studies have consistently shown increased frequency, extent and severity of periodontitis among diabetic adults [4]. More recently, some controlled clinical trials have also suggested that periodontal treatment could improve glycaemic control in diabetic patients [5-10]. We previously conducted a systematic review of the literature and found that results were conflicting across trials [11].

This could be attributed to considerable differences in methodology and also in the sample sizes and compositions of the groups included in the studies. The study by Jones et al. [6] was the best quality study that we assessed in the meta-analysis but the subjects enrolled in this trial were highly specific (American veterans, mainly males, smokers, with poorly controlled diabetes). Other studies showed evidence of methodological deficiencies (mainly small sample sizes). Further, the majority of clinical trials on this topic have included subjects with poorly controlled diabetes (HbA1c > 9%) [11]. We argue that periodontal treatment to improve glycaemic control in diabetic patients would be more relevant among patients with moderately poor glycaemic control (HbA1c between 7.0 and 9.5%). Interventions other than periodontal treatment (e.g. adequate medical treatment) are likely to be more effective in reducing HbA1c levels in poorly controlled diabetic patients.

Our systematic review emphasized the need to conduct a well-designed randomized controlled trial in a European population, among patients with suboptimal glycated haemoglobin levels, according to clinical recommendations for the treatment of chronic periodontitis in diabetic subjects.

## Methods

The DIAPERIO trial is an open-label, 13-week follow-up, randomized, controlled trial. The design specifies a balanced (1:1) treatment allocation.

### Objectives

The main objective of this study is to assess whether periodontal treatment could lead to a decrease in glycated haemoglobin (HbA1c) levels in metabolically unbalanced diabetic patients suffering from periodontitis. We will therefore test the null hypothesis that periodontal treatment does not reduce the HbA1c level in metabolically unbalanced diabetic patients suffering from periodontitis.

The secondary objectives of this study are to assess, among metabolically unbalanced diabetic patients suffering from periodontitis:

• whether periodontal treatment could lead to a decrease in fructosamine levels,

• whether periodontal treatment could lead to an improvement in quality of life.

### Study participants

#### Setting and location

Volunteers will be recruited in the Diabetology Departments of two University Hospitals of south-western France (Toulouse-Rangueil Teaching Hospital and Bordeaux-Haut-l'Eveque Teaching Hospital). Subjects will be selected in two steps: a screening visit at the Diabetology Department, and an inclusion visit at the Dental Care Department of the same University Hospital. Periodontal treatments and follow-up visits will be performed in the Dental Care Departments (Figure 1).

**Figure 1 F1:**
[figure not shown]
**Study timelines**.

#### Eligibility criteria

Eligibility criteria will be assessed in the Diabetology and Dental Care departments at V0 and V1 respectively.

##### At V0 (Diabetology Department)

During the study period, all consecutive patients who consult in the Diabetology Departments will be screened for possible inclusion in the trial. Pre-inclusion and non-inclusion criteria will be checked by diabetologists using a standardized questionnaire.

##### Pre-inclusion criteria (V0)

To be pre-included, patients will have to:

- be aged 18 years or older (male or female),

- be affiliated to a public health system,

- be diagnosed as having had type 1 or 2 diabetes for at least one year before V0,

- have a last known value of HbA1c, measured within three months prior V0, between 6.8% and 9.7%,

- have received stable antidiabetic therapy (no changes to diet, medication, dosage or formulation) during the three months preceding V0,

- have at least six natural permanent teeth,

- be available for all study visits over three months in the Dental Care Departments (V1 to V6),

- be able to give their written informed consent.

##### Non-inclusion criteria (V0)

Several non-inclusion criteria will also be checked in the Diabetology Departments. Patients will not qualify for enrolment if they:

- have severe difficulties in understanding written and spoken French,

- are participating in another intervention study,

- do not have a known value of HbA1c level,

- have a known diabetes complication leading to planned hospitalization within 4 months after the screening visit,

- have a known pathological condition leading to planned hospitalization within 4 months after the screening visit,

- are suffering from one or more known infectious diseases (HIV, hepatitis, infectious mononucleosis),

- are suffering from known clinically significant renal disease (creatinine clearance <60 ml/min), or liver disease,

- have known phenylketonuria,

- have a known risk of endocarditis,

- have a permanent pacemaker,

- suffer from a chronic disorder that requires chronic or intermittent use of corticosteroids and/or antibiotics,

- are taking antithrombotic treatment,

- have known hypersensitivity to chlorhexidine gluconate,

- have known contraindications to both amoxicillin and clindamycin,

- for females: are pregnant or intending to become pregnant, or lactating.

Subjects satisfying the pre-inclusion criteria and exempt from the non-inclusion criteria at V0 will be given the possibility of further participating in the trial and will be given a scheduled appointment at the Dental Care Department (V1) within 3 weeks after V0 (Figure 1).

##### At V1 (Dental Care Department)

Non-inclusion and inclusion criteria will be checked by trained dentists-examiners, using a standardized questionnaire and a calibrated examination method.

##### Non-inclusion criteria (V1)

At this stage, patients will not qualify for enrolment if they present at least one of the following: acute oral infection, acute oral pain (including pulpitis), suspicious oral mucosal lesion, severe oral inflammation unrelated to periodontal conditions, or need for immediate tooth extractions. Patients with any of the above problems will be offered treatment in the Dental Care Department as routine patients. Inclusion will be reconsidered after remission of the condition(s).

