##### Inclusion criteria (V1)

Final inclusion will be decided at the Dental Care Departments, during the inclusion visit (V1). The criteria for inclusion are:

- written informed consent,

- no change relative to pre-inclusion criteria and non-inclusion criteria since V0,

- patient with periodontitis. Periodontitis is defined by the presence of one site with periodontal probing depth (PPD) ≥ 4 millimetres and clinical attachment level (CAL) ≥ 3 millimetres on at least 4 teeth.

- patient with HbA1c level ≥ 7.0% and ≤ 9.5%. Blood samples will be taken during V1, after periodontal assessment. Thus blood will only be taken from patients with periodontitis.

Subjects fulfilling all the inclusion criteria and none of the non-inclusion criteria at V1 will be randomized and will be given a scheduled appointment at the Dental Care Department, within 10 days for the treatment group (V2), and between 21 and 31 days from V1 for the control group (V3) (Figure 1).

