### Outcomes

#### HbA1c

The primary outcome of the DIAPERIO trial will be the difference in change of HbA1c from V1 to V4 between the two groups. The HbA1c level is proportional to average blood glucose concentration over the previous 1 to 3 months.

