### Statistical methods

Sample size calculation was based on detecting a difference of 0.5% in HbA1c change from baseline between the two groups. Assuming a standard deviation of 1.0% and using a 2-sided test at 5% significance level, 64 participants per group would yield 80% power. Anticipating a 15% dropout rate, the target sample size was thus planned at 150 participants.

Baseline characteristics by group will be presented as mean (SD) for continuous variables and tallied for categorical variables. The intention-to-treat population will consist of all randomized subjects whereas the evaluable population will consist of subjects from the intention-to-treat population who complete the 3-months follow-up. Descriptive statistics will be provided for the intention-to-treat population.

All primary analyses will be performed according to intention-to-treat principles, on the evaluable population (i.e. all patients with initial (V1) and final (V4) HbA1c measurements), regardless of the subject's presence at intermediate visits or his/her degree of compliance with the treatment. Subjects with missing initial or final HbA1c measurements will be excluded from the analysis. The main analysis will be a comparison between the two study groups concerning the change in the HbA1c levels from baseline to 3 months in an analysis of covariance (ANCOVA) model, adjusted for the baseline HbA1c level and clinical centre. Residual values will be examined for an approximate normal distribution. If HbA1c values are highly skewed, a transformation or non-parametric method will be used instead [15].

The data will also be analysed using the "per protocol" approach. Here the analysis will be restricted to participants who were compliant with the treatment protocol (SRP, ATB and OHI).

In addition to the primary analysis, five binary outcomes for HbA1c at 3 months (a relative decrease of ≥10%, a three-month level of < 7%, an absolute decrease of ≥0.5%, a relative increase of ≥10% and an absolute increase of ≥0.5%) will be evaluated in logistic regression models adjusted for the baseline HbA1c level and clinical centre [16].

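### Scaling and root planing or an antibiotic course shortly before V1 is no bar to entry, so recently treated patients can attenuate the treatment difference

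*Protocol article*

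**What the plan says.** All references are to the Methods of the protocol article.

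- **Non-inclusion criteria (V1).** Acute oral infection, acute oral pain, a suspicious mucosal lesion, severe inflammation not related to the periodontium, and the need for immediate extractions bar entry. These patients are offered routine treatment, after which "Inclusion will be reconsidered after remission of the condition(s". No interval and no repeat of V0 is mentioned.
- **Non-inclusion criteria (V0).** The only criterion on antibiotic use covers patients who "suffer from a chronic disorder that requires chronic or intermittent use of corticosteroids and/or antibiotics". A single recent course falls outside it. V1 is to be scheduled within 3 weeks of V0.
- **Pre-inclusion criteria (V0).** The only look-back on treatment is three months of stable antidiabetic therapy before V0.
- **Inclusion criteria (V1).** Periodontitis on at least 4 teeth and "patient with HbA1c level ≥ 7.0% and ≤ 9.5" per cent are required. The requirement that nothing has changed since V0 refers back to the V0 lists and adds no dental or antibiotic look-back.
- **Intervention.** The tested treatment is scaling and root planing, a systemic antibiotic and oral health instructions.
- **Outcomes, HbA1c.** "The HbA1c level is proportional to average blood glucose concentration over the previous 1 to 3 months".

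**The concern.** The trial asks whether periodontal treatment lowers HbA1c over about three months. The protocol protects that question against recent changes in antidiabetic therapy, but not against recent use of the components under test. A patient who was scaled a few weeks before V1 and still has qualifying sites on four teeth is eligible. The section on systemic antibiotherapy says that French authorities recommend antibiotics for metabolically unbalanced diabetic patients receiving periodontal treatment, so earlier periodontal care may have included both main components.

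Such a patient in the treatment group may have less benefit left to obtain. In the control group the patient has already had some or all of the treatment that the control period is meant to withhold. Either way, what immediate trial treatment adds over delay is smaller. Randomisation spreads these patients evenly, and the ANCOVA adjusts for baseline HbA1c, but neither restores the lost contrast. At stake is power, in a trial planned at 80% with no reserve.

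**Working it through.** **Inputs** (Statistical methods): "detecting a difference of 0.5% in HbA1c change from baseline between the two groups"; "Assuming a standard deviation of 1.0" per cent; "using a 2-sided test at 5% significance level"; "64 participants per group would yield 80% power"; 15% dropout; 150 in total.

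**Step 1: the plan's own figure.** For a two-sample t-test with difference 0.5 and SD 1.0, the required size is 63.8, so 64 per group, and power at 64 is 80.1%. The normal approximation gives 63 per group, and 80.7% power at 64. The figure reproduces. With dropout, 128 / 0.85 = 150.6, against 150 planned; 150 × 0.85 = 127.5 evaluable against 128 needed. There is no arithmetic error and no spare capacity.

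**Step 2: a shared drift.** Suppose a share f of patients in both arms has an HbA1c fall of 0.5 still under way after V1 because of earlier care, independent of their other variation. The mean difference stays 0.5. Only the variance changes:

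SD = √(1.0² + f(1 − f) × 0.5²)

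| f | SD | Power, t-test, 64 per group |
|---|---|---|
| 5% | 1.006 | 79.7% |
| 10% | 1.011 | 79.3% |
| 20% | 1.020 | 78.6% |
| 30% | 1.026 | 78.1% |

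So carry-over in the baseline costs about 2 percentage points of power at most over this range.

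**Step 3: less left to gain.** Suppose a share f had such care recently enough to matter and loses a fraction c of the treatment effect. Then

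average difference = 0.5 × (1 − f × c)

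with the SD held at 1.0. Neither f nor c is in the document; the values below are assumptions. Example: f = 10%, c = 50% gives 0.5 × 0.95 = 0.475.

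| f | c | Difference | Power, t-test | Power, normal approximation |
|---|---|---|---|---|
| 5% | 50% | 0.4875 | 78.1% | 78.7% |
| 10% | 50% | 0.475 | 76.0% | 76.6% |
| 20% | 50% | 0.45 | 71.4% | 72.1% |
| 5% | 100% | 0.475 | 76.0% | 76.6% |
| 10% | 100% | 0.45 | 71.4% | 72.1% |
| 20% | 100% | 0.40 | 61.2% | 61.9% |

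The rows with c = 100% are an upper bound on the loss for the given share.

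**The case against.** A reader might infer that carry-over in the V1 HbA1c itself dilutes or biases the comparison. The documents do not support this. The exposure precedes randomisation, so it is balanced in expectation. A drift common to both arms cancels, as step 2 shows. ANCOVA on baseline HbA1c does not need a stable baseline to be unbiased under randomisation.

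The other side has more to say, and much of it stands:

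- Most conditions on the V1 list are not treated with the tested intervention. Relieving pulpitis or extracting a tooth is not full-mouth scaling and root planing, and the inflammation listed is expressly of non-periodontal origin. Acute care may include antibiotics, but the article does not say how often. The re-entry route alone is therefore the weaker part of the point; the missing look-back for earlier scaling and root planing is the stronger.
- Every participant must still have periodontitis on at least 4 teeth and an HbA1c in range at V1, after any earlier care. Complete loss of effect is therefore an extreme assumption.
- Re-entry is a renewed eligibility judgement, not automatic admission, and the V0 criteria must still hold.
- Accepting patients with ordinary prior dental care can be defended as a broader population.

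It might also be said that the full protocol contains a look-back which the article omits. That cannot be ruled out. But the article itemises its criteria down to phenylketonuria and pacemakers and states the re-entry rule outright, so the gap is in the criteria as printed.

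None of this answers the remaining point: the requirement for residual disease limits the loss of achievable effect but does not exclude it.

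**Conclusion.** The point holds in a limited form. As printed, the criteria admit patients who had components of the tested treatment shortly before V1, and set no interval for re-entry after acute oral care. The consequence is possible attenuation of the between-group difference, plus a little extra variance. The arm comparison stays unbiased, and the sample-size calculation is correct.

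The size rests on two unknowns: the share of patients affected and the part of the effect they lose. On the t-test basis that reproduces the plan's 64 per group, power falls from 80% to 78%, 76% or 71% for shares of 5%, 10% or 20% with half the effect lost, and to 76%, 71% or 61% with all of it lost. The normal approximation gives values up to about one percentage point higher. If few patients are affected, the loss is negligible. The lowest figures should not be read as the expected loss. The change is worth making because it is cheap and follows the protocol's own logic for antidiabetic therapy; the trial's validity does not depend on it.

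**What to change.** These changes concern trial entry only; the routine care of these patients is unchanged.

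1. Add to the non-inclusion criteria: scaling and root planing, or a systemic antibiotic course, within the 3 months before V1. This matches the upper end of the protocol's HbA1c window and its three-month rule for antidiabetic therapy.
2. Apply the same interval to re-entry after acute oral treatment. Re-check the V0 criteria, including the screening HbA1c and stable therapy, because V1 must fall within 3 weeks of V0 and a deferred patient will be outside that window.
3. Add one question on earlier periodontal treatment and antibiotics to the existing standardised questionnaires.

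The cost is one sentence in each of two criteria lists, the questionnaire item, and some patients who enter later or not at all. That number scales with the same unknown share as the benefit: 0.05 × 150 = 7.5, so about 8 patients, at 5%, and 0.20 × 150 = 30 at 20%. If recruitment at two centres cannot bear this, a weaker alternative is to record prior exposure and examine it in a sensitivity analysis. That excludes no one, but it does not restore lost power.

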##### Inclusion criteria (V1)

Final inclusion will be decided at the Dental Care Departments, during the inclusion visit (V1). The criteria for inclusion are:

- written informed consent,

- no change relative to pre-inclusion criteria and non-inclusion criteria since V0,

- patient with periodontitis. Periodontitis is defined by the presence of one site with periodontal probing depth (PPD) ≥ 4 millimetres and clinical attachment level (CAL) ≥ 3 millimetres on at least 4 teeth.

- patient with HbA1c level ≥ 7.0% and ≤ 9.5%. Blood samples will be taken during V1, after periodontal assessment. Thus blood will only be taken from patients with periodontitis.

Subjects fulfilling all the inclusion criteria and none of the non-inclusion criteria at V1 will be randomized and will be given a scheduled appointment at the Dental Care Department, within 10 days for the treatment group (V2), and between 21 and 31 days from V1 for the control group (V3) (Figure 1).

### Intervention

Periodontal treatment will include non-surgical scaling and root planing, systemic antibiotherapy, and oral health instructions.

#### • Scaling and root planing (SRP)

This will be performed at V2 for the treatment group, and at V5 for the control group (Figure 1). Non-surgical periodontal therapy will be performed during a 2-hour, single-session, full-mouth ultrasonic debridement by trained dentists-examiners, who will receive special training from a periodontist prior to the beginning of the study.

Disclosing solution will be used to visualize the plaque for the clinician. Then scaling and root planing will involve removal of supra- and sub-gingival plaque from all tooth surfaces, and removal of supra- and sub-gingival calculus with both ultrasonic and hand instruments (Gracey curettes). Mechanical debridement will be performed under local anaesthesia if necessary. Scaling and root planing will be combined with subgingival irrigation using an antiseptic mouth rinse (chlorhexidine 0.12%). Finally, the coronal and radicular surfaces of the teeth will be polished.

#### • Systemic antibiotherapy (ATB)

The French health authorities recommend the prescription of systemic antibiotherapy for metabolically unbalanced diabetic patients receiving periodontal treatment [12,13]. On primary intention, capsules of 500 mg amoxicillin will be prescribed to patients 3 times a day (morning, midday and evening) for 7 days. Two boxes of 12 capsules will be given to the patients after scaling and root planing (at V2 for the treatment group and at V5 for the control group). In case of contraindication to beta-lactam antibiotics, capsules of 300 mg clindamycin will be prescribed to patients twice a day (morning and evening) for 7 days. One box of 16 capsules will be given to the patients after scaling and root planing (at V2 for the treatment group and at V5 for the control group). These antibiotics are recommended by French health authorities for the treatment of chronic periodontitis in diabetic patients [13].

